## Abstract

**Background:**

An increasing number of children are suffering from brain damage-related visual processing dysfunctions (VPD). There is currently a lack of evidence-based intervention methods that can be used early in development. We developed a visual intervention protocol suitable from 1 year of age. The protocol is structured, comprehensive and individually adaptive, and is paired with quantitative outcome assessments. Our aim is to investigate the effectiveness of this first visual intervention program for young children with (a risk of) VPD.

**Methods:**

This is a single-blind, placebo-controlled trial that is embedded within standard clinical care. The study population consists of 100 children born very or extremely preterm (< 30 weeks) at 1 year of corrected age (CA), of whom 50% are expected to have VPD. First, children undergo a visual screening at 1 year CA. If they are classified as being at risk of VPD, they are referred to standard care, which involves an ophthalmic and visual function assessment and a (newly developed) visual intervention program. This program consists of a general protocol (standardized and similar for all children) and a supplement protocol (adapted to the specific needs of the child). Children are randomly allocated to an intervention group (starting upon inclusion at 1 year CA) or a control group (postponed: starting at 2 years CA). The control group will receive a placebo treatment. The effectiveness of early visual intervention will be examined with follow-up visual and neurocognitive assessments after 1 year (upon completion of the direct intervention) and after 2 years (upon completion of the postponed intervention).

**Discussion:**

Through this randomized controlled trial we will establish the effectiveness of a new and early visual intervention program. Combining a general and supplement protocol enables both structured comparisons between participants and groups, and custom habilitation that is tailored to a child’s specific needs. The design ensures that all included children will benefit from participation by advancing the age at which they start receiving an intervention. We expect results to be applicable to the overall population of children with (a risk of) VPD early in life.

**Trial registration:**

Netherlands Trial Register: NTR6952. Registered 19 January 2018.

## Background

Over the past decades, survival rates of children with neurodevelopmental disorders or who experienced adverse perinatal events (e.g., preterm birth, hypoxia/ischemia, cerebral hemorrhages) have increased due to the intensive, high quality care that they receive. As a consequence, the prevalence of children with brain damage has also increased. Since approximately 40% of the brain is involved in processing visual information, there is a high likelihood that these children will develop visual dysfunctions. Visual dysfunctions with a cerebral origin are generally called cerebral visual impairments (CVI) and have become common in children – conservative estimates range from 10 to 22 cases per 10,000 births in developed countries, to 40 per 10,000 births in developing countries [1]. CVI are now the primary cause of low vision in children [2, 3]. The visual system consists of an extensive network that involves both ocular and subcortical structures and numerous brain areas, including higher-order parietal and frontal areas. Consequently, children with brain damage-related visual impairments, or CVI, are a heterogeneous population that can suffer from a variety of problems – from lower-order visual sensory and oculomotor deficits, to higher-order visual perception difficulties. What they have in common on a functional level are challenges with detecting, attending to and processing incoming visual information, i.e., visual processing dysfunctions (VPD). VPD include issues with orienting and maintaining visual attention, detecting and perceiving specific visual features (e.g., colors, forms, motion) as well as with giving meaning to what is perceived and using the visual input for behavior. These visual processing functions can be considered prerequisites for higher-order visual perception functions, e.g., visual recognition and visuospatial orientation. Unlike such perception problems, which cannot reliably be assessed before school age, signs of VPD can be detected at earlier developmental stages. Given that early visual dysfunctions can severely delay or disrupt neurocognitive, motor and behavioral development [4–6], VPD particularly affect young children.

To alleviate early-onset problems, prevent later growing-into-deficit, and maximize developmental opportunities, detection and habilitation of VPD early in life is crucial [7, 8]. Early in development, high levels of cerebral plasticity may enable recovery or take-over of function on a structural level, whereas early and diverse visual experiences may enhance visual development on a functional level. Therefore, it is assumed that the sooner visual habilitation programs start, the higher the likelihood that they will stimulate and improve visual processing development. Although there are a large number of infant studies regarding early detection of visual dysfunctions that rely on this assumption, the effectiveness of early interventions in the visual domain has never been proven.

Early habilitation starts with early detection. Before the age of 4–5 years, it used to be challenging to assess the functional consequences of damage to the brain’s visual system. There have been advances in the early detection of (a risk of) visual problems, for example, the early assessment of basic visual function in neonates as early as 31 weeks of gestation [9] and a functional vision battery with cognitive and integrative aspects for use between 1 and 4 years of age [10]. These batteries involve various aspects of visual function and rely on behavioral observations. In addition, more quantitative, computer-based methods have been developed such as an eye tracking-based task for attention in toddlers [11]. Building on these innovations, our group developed a method to quantify visual processing efficiency in a non-verbal manner in children, using an eye tracking-based approach [12, 13]. We showed that children with (a high risk of) brain damage or dysfunction (e.g., children with visual disorders or children born extremely preterm) are prone to developing VPD [14–16]. These VPD were particularly strongly correlated with diagnosed CVI [17, 18]. These innovative early and non-verbal assessments can fulfill the need for scientifically strong psychometric tools to evaluate the effectiveness of early intervention. Besides providing an early characterization of VPD that was previously unavailable, they also open up the possibility to monitor or habilitate VPD at a young age. One can even argue that early detection of problems is only useful if it leads to advancing support and habilitation. Hence, the essential next step in the field of pediatric visual dysfunctions is to provide affected children with effective early intervention programs.

A major problem is that there is no evidence-based intervention for VPD from 1 year of age – this area is severely understudied [19] and quality of evidence is low [20–22]. Available (visual) interventions lack a standardized approach and/or systematic objective evaluation [23–25], and ideas about their effectiveness merely stem from clinical impressions, not from randomized and carefully controlled studies. The available evidence has predominantly been found in older children, for a limited range of visual functions (i.e., visual acuity and/or contrast sensitivity) [26], without incorporation of functional vision measures, using only stimulation and no training [24, 26], and without objective outcome measures. Studies that did use a comprehensive and structured training approach had a small sample size [27, 28]. Although these existing studies provide important information on the approaches and possibilities to habilitate visual problems, the effectiveness of visual intervention programs for children younger than 4 years has not yet been investigated with a randomized controlled trial (RCT).

VPD in children can arise from many different conditions, e.g., perinatal asphyxia or hypoxia, focal lesions, cranial trauma, infections, or hemorrhages. Therefore, the general population with VPD is a highly heterogeneous group of children. In the present study, we focus on children born very or extremely preterm (i.e., born < 30 weeks of gestation) from 1 year of corrected age (CA). In an ongoing longitudinal study, we found elevated risks of visual attention and processing problems in this population [15, 16], driving the urgency for interventions. However, we expect outcomes to be applicable to other young children at risk of brain damage-related VPD. After positive results have been obtained, the visual intervention program can be investigated in other risk groups.

The aim of this study is to investigate the effectiveness of early intervention of VPD in children born very or extremely preterm from 1 year CA. To this end, we developed a structured yet individually tailored visual intervention protocol. We will test its effectiveness in enhancing visual development with a RCT. Unique features of the presented approach are the objective outcome measures assessed from a young age, broad quantitative and qualitative data collection to assess the full spectrum of visual functions and neurodevelopment, and embedding of the project within standard neonatal and visual clinical care. This protocol was written in accordance with the Standard Protocol Items: Recommendations for Intervention Trials (SPIRIT) guidelines. Additional file 1 contains the SPIRIT checklist.

## Methods

### Study design

Randomized single-blind, placebo-controlled intervention study (RCT), embedded within standard clinical care.

### Study setting

The study will be executed at the Neonatology Department of an academic medical center, in collaboration with the Department of Pediatric Ophthalmology and with four regional centers of a center of expertise for blind and partially sighted people that provides visual diagnostics and (re)habilitation.

### Participant characteristics and timeline

It is expected that 25–50% of the very preterm population is at risk of VPD at 1 year CA [15, 16]. Therefore, all infants who have been born before 30 weeks gestational age and who participate in the clinical follow-up program of the Department of Neonatology, will be available for inclusion around 1 year CA. We aim to include children from 1 year CA, born < 30 weeks of gestation (about 50% are expected to be at risk of VPD, and eligible for the intervention) (*n* = 100) and children born at term without VPD from 1 year of age, to add to an existing database of typically developing children (healthy control group) (*n* = 100). The study population will be divided into three groups, with two subgroups – Group 1: children born very preterm from 1 year CA, without a risk of VPD; Group 2: children born very preterm from 1 year CA, with a risk of VPD (50% will receive direct visual intervention (group 2A, intervention group) and 50% will receive postponed visual intervention (group 2B, control group); Group 3: children born at term without a risk of VPD.

### Eligibility criteria

Inclusion criteria
Born < 30 weeks gestational ageAge at inclusion of 1 year CA (+/− 2 months)

Exclusion criteria
Visual acuity below 0.05 (Snellen equivalent); the visual screening (i.e., eye tracking-based exam) is designed to be visible with a visual acuity of 0.05 or higherHigh chance of epileptic activity during assessment; more than two attacks in the previous year or when using the anti-epileptic vigabatrin (which may lead to visual dysfunction)Retinopathy of prematurity of grade 3 or higher, assessed by a pediatric ophthalmologist, as this will account for their visual dysfunction

### Study procedures

Figure 1 outlines the general time schedule of the study. Figure 2 outlines the flow of assessments and interventions for study participants.

**Fig. 1 Fig1:**
[figure not shown]
Time schedule of enrolment, interventions, and assessments

**Fig. 2 Fig2:**
[figure not shown]
Flow diagram

#### Participant inclusion and baseline screening

Children born at < 30 weeks gestational age will be recruited around the CA of 1 year at the Department of Neonatology of an academic medical center. After obtaining written informed consent (Additional file 2), a visual screening is performed to identify the prevalence and nature of VPD (for details, see ‘Data collection methods’). The first part of the screening consists of an eye tracking-based assessment of visual attention and processing. The visual assessment results are compared to normative references to identify the children with a risk of VPD. The second part of the screening is a checklist to identify common neurological risk factors for VPD, and that is completed by the neonatologists.

Children who are identified as being at risk of VPD will first undergo an orthoptic and ophthalmic exam at the Department Pediatric Ophthalmology (including refraction, ocular alignment). Next, they will be referred to a visual advisory and rehabilitation center in order to receive standard care, consisting of a visual function assessment (VFA) and a visual intervention program. The VFA is used to evaluate visual sensory functions (e.g., visual acuity, visual field, contrast sensitivity, ocular motility) and to observe the functional visual behavior of the child. This assessment is performed by experienced orthoptists, optometrists and behavioral therapists, and together they will determine the visual level of the child [5, 29] according to the following categories:
A.Profound visual dysfunction/legally blind (mainly responding to light)B.Severe visual dysfunction, passive attentional system (reactions to stimuli do not reach normative levels, child does not actively search for visual stimulation, low recognition)C.Moderate visual dysfunction/basic perception (active visual attention system and basic visual recognition)D.Mild visual dysfunction, subnormal visual function (functioning at the lower bound of normal)

#### Intervention

For a detailed outline of the visual rehabilitation protocol we refer to the section ‘Intervention: a visual habilitation protocol’ and to Additional file 3: template visual intervention protocol. To reliably examine the effectiveness of the visual intervention program with an RCT, children who are at risk of VPD will be randomly allocated to one of two groups, as follows:
*Intervention group (direct)*

This group consists of very preterm children who are at risk of VPD and who will start the visual intervention program upon referral to the visual rehabilitation center (i.e., around 1 year CA). The program consists of a general protocol (standardized across participants) and a supplement protocol (tailored to the child’s specific VPD), and lasts ~ 1 year.
2.*Control group (postponed and placebo)*

This group consists of very preterm children who are also at risk of VPD, but for whom the visual intervention program will be postponed for the duration of 1 year. These children will be placed on a waiting list for the duration of the direct visual intervention (i.e., ~ 1 year). During this first year, they will receive a placebo intervention involving general developmental support that is aimed at monitoring the child’s developmental progress without providing specific visual habilitation. As soon as the follow-up assessments of the direct intervention group are completed, children in the control group will start visual intervention (i.e., around 2 years CA).

Importantly, this study design ensures that all children at risk of VPD will receive visual intervention at an earlier age than is the case in current standard care (i.e., where only a small number of young children will be referred based on obvious ocular disorders, and others will not receive interventions before the age of 4–6 years), while the RCT design enables a reliable and controlled comparison of the effectiveness of visual intervention within this group.

#### Follow-up after 1 year

One year after inclusion, the children at risk of VPD will repeat the visual function assessments, and all included children (with and without VPD risk) will repeat the eye tracking-based visual screening and undergo a neurodevelopmental assessment (that is standard care at most Neonatology departments, from 2 years CA). That way, the specific effects of early visual intervention on visual processing and neurocognitive development are compared and evaluated.

#### Postponed intervention

After the first follow-up, the children in the postponed intervention group will start their visual intervention program, which will also be evaluated 1 year later. In addition, the results of the visual screening are again evaluated for all children, to identify new cases with a risk of VPD who will then also qualify to start visual intervention. Differences in effectiveness of direct and postponed early visual intervention are assessed. The intervention study will have a duration of either 1 or 2 years, depending on the visual intervention group.

### Data collection methods

#### Baseline (T0)

Medical and demographic information will be extracted from the medical records available at the academic medical center.

##### Visual screening – A0

All included children will be screened for a risk of VPD, which consists of (1) an eye tracking-based assessment and (2) a neurological checklist. The eye tracking-based assessment is used to measure visual attention and processing functions. The assessment will be combined with an existing appointment for standard outpatient visits at the Neonatology Department when the child is ~ 1 year CA (T0) and 2 years CA (T1). During this assessment, children sit in front of the eye tracker monitor at a distance of approximately 60 cm, either independently, on the lap of their parent or in a pram. They do not receive verbal instructions and their body and head position is not restricted. The assessments are conducted in a quiet room with ambient light conditions. Visual stimuli (images and movies) are presented on the monitor to engage the reflexive orienting eye movements of the child, while simultaneously the eye positions are recorded over time using infrared cornea reflection (Tobii T60 XL or Tobii X3, Tobii Corporation, Danderyd, Sweden). That way, the child’s eye movement responses to various types of visual information (i.e., contrast, color, motion and form) are automatically recorded. These viewing behavior responses indicate whether and how fast a specific stimulus was detected and looked at. From these responses, the number of detected stimuli and the reaction time to fixation (RTF) of a stimulus are calculated. RTF is a measure for the timing of detecting and processing visual information and is the main study parameter [12, 13, 30, 31]. Total test duration is approximately 15 min. The child’s viewing behavior parameters per visual stimulus are analyzed and compared with normative data, i.e., developmental trajectories of an existing database of healthy control children, born at term to identify abnormal detection and timing of processing of the visual stimuli. This results in a classification of normal and abnormal visual attention and processing functions.

Second, medical specialists examine the child’s medical history for the presence of neurological risk factors for VPD in the context of prematurity [32–35], i.e., moderate-severe damage on neonatal MRI scans; cerebral palsy, unilateral/bilateral hemiplegia/diplegia; infantile esotropia/convergent strabismus or nystagmus; and deviating head circumference (> 1 SD in 12 months).

##### Inventories for daily life visual functioning – B0

The Participation and Activities Inventory – Children and Youth (PAI-CY) 0–2 questionnaire [36] will be filled in by parents upon inclusion. This questionnaire assesses daily visual functioning in seven domains. Originally developed as a list to identify participation and activity needs, it can also be used to investigate and monitor intervention needs of visually impaired young children. It is the only available patient-reported visual outcome measure for young children and has satisfactory psychometric properties [37].

##### Determining the risk of VPD

The risk of VPD is determined based on the baseline screening: abnormal viewing behavior, indicated by abnormal RTF values on one or more visual stimuli and/or the presence of at least one neurological risk factor for VPD. The children at risk of VPD are referred to standard care for children with suspected visual dysfunctions, i.e., they will undergo an ophthalmic exam to evaluate eye and orthoptic function and they will become clients of the visual advisory and rehabilitation center where they undergo a visual function assessment and are enrolled in the visual intervention program.

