### Outcome measures

To answer our main research question about the effectiveness of early visual intervention in young preterm children, we will compare visual outcomes between the intervention and control group. We will analyze results from the eye tracking-based visual assessment and the additional VFAs at baseline and at yearly follow-up measurements. Primary outcomes are the changes in visual parameters after the duration of the intervention study (i.e., from baseline to follow-up T1 and/or T2), namely quantitative visual parameters (eye tracking-based visual detection and viewing reaction times) and VFA (visual acuity, contrast sensitivity, visual field, ocular motility).

Endpoints are the changes in these parameters after the visual intervention program. These parameters are chosen since their combination provides quantitative and objective results about functional viewing behavior (the eye tracking-based assessment) and clinically relevant visual function outcomes (i.e., the VFAs). In addition, we will compare the effectiveness of direct (at 1 year CA) versus postponed visual habilitation (at 2 years CA) by comparing visual outcomes between these groups at T2.

Secondary outcomes are the neurodevelopmental level at the first follow-up (T1) and results from parental questionnaires about daily visual functioning at T1 and/or T2, i.e., total score, cognitive and motor sub scores of the neurocognitive assessment with Bayley Scales of Infant and Toddler Development (Bayley-III-NL) and total score and sub scores per visual domain of the PAI-CY 0–2 Inventory (i.e., attachment, stimulus processing, orientation, play, mobility, communication). These measures were chosen because Bayley-III-NL is the only available neurocognitive assessment for children at this age, and the PAI-CY 0–2 Inventory is the only available parental questionnaire about daily (visual) behavior at this age.

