### Sample size calculation

Each year, approximately 200 children are born before 30 weeks of gestation and admitted to the Neonatal Intensive Care Unit at the academic medical center in Rotterdam, the Netherlands. Based on previous research with this population we expect an inclusion rate of ~ 50%. Therefore, we expect to include at least 100 children at 1 year CA. There are no thorough estimates of the prevalence of VPD in preterm children. A previous study using the eye tracking-based assessment in extremely preterm children identified visual processing delays in 48% of preterm children without evidence for brain damage [16], and in 9% to 23% of children in a cross section of the preterm population at 1 year CA [15]. In addition, between 25% and 33% of children with CVI have prematurity as a contributing factor [32]. However, the prevalence of risk factors for VPD in our study population (often with brain damage and perinatal events) is much higher than 50%. Therefore, we expect that each year at least 50 newborn preterm children from the Neonatology Department (i.e., 50%) are at risk of VPD and thus eligible for inclusion in the intervention study.

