### Randomization and intervention allocation

Prior to recruitment of participants, a randomization scheme has been designed in which the order of visual intervention groups (either direct or postponed) is randomized using an online tool (Sealed Envelope Ltd. 2016; https://www.sealedenvelope.com/simple-randomiser/v1/lists).

Randomization is blocked to ensure a balance in sample size across groups over time and stratified to control and balance the influence of covariates [47]. Covariates in the current study are the presence of brain damage and gestational age (< 28 weeks or 28–30 weeks).

After this computer-generated randomization, preterm children who are classified as being at risk of VPD will be assigned a participant number and concurrently be allocated to one of the visual intervention programs. The order of allocation corresponds with the date and order of inclusion. This allocation will be done by the principal investigator and remains concealed to all other investigators, the participating children, and their parents. All participant numbers will be separately placed in opaque envelopes that contain a note with the assigned visual intervention group. Revealing the group allocation to parents will be done by opening the opaque envelopes in their presence.

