### Statistical analyses

#### Sample size calculation

To answer our primary research question about the effectiveness of early visual intervention programs on visual attention and processing functions in preterm children at risk of VPD, we use a repeated measures analysis of variance (ANOVA) for the parameter RTF as primary analysis. An a priori power analysis provided a recommended total sample size of 32 children (and an actual power of 0.81 and a critical F of 4.17).

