#### Effectiveness of visual intervention program

In children at risk of VPD who have been allocated to a visual intervention group, differences in viewing behavior parameter RTF between T0 and T1 are analyzed with a Repeated Measures ANOVA. A *p* value of 0.05 will be considered statistically significant. Covariates are the medical (perinatal and ophthalmic) and demographic factors and the repeated measures analyses will be done with and without them to obtain their contribution to the main effect. All analyses are done according to the intention-to-treat principle.

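### Children can be randomised with normal reaction times on every stimulus, yet the primary analysis of reaction-time change does not separate them from children with a measured deficit

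*Protocol article*

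**What the plan says.** - **Entry.** Under Determining the risk of VPD, a child qualifies on "abnormal RTF values on one or more visual stimuli and/or the presence of at least one neurological risk factor for VPD". Either route alone is enough.
- **Checklist.** Under Visual screening – A0, "medical specialists examine the child’s medical history for the presence of neurological risk factors for VPD in the context of prematurity". The items are neonatal MRI damage, cerebral palsy or related motor signs, strabismus or nystagmus, and deviating head circumference. None is an RTF measurement.
- **Allocation.** Under Randomization and intervention allocation, "preterm children who are classified as being at risk of VPD will be assigned a participant number and concurrently be allocated", with no distinction by entry route. On stratification: "Covariates in the current study are the presence of brain damage and gestational age".
- **Primary analysis.** The power paragraph under Statistical analyses states that "we use a repeated measures analysis of variance (ANOVA) for the parameter RTF as primary analysis". The section on effectiveness adds that "differences in viewing behavior parameter RTF between T0 and T1 are analyzed with a Repeated Measures ANOVA". Its covariates are medical (perinatal and ophthalmic) and demographic factors. Baseline RTF status is not named.
- **Expected frequencies.** The Sample size calculation section under Methods gives eye-tracking delays in 9% to 23% of a preterm cross section at 1 year corrected age, and in 48% of a preterm group without evidence of brain damage. It adds that "the prevalence of risk factors for VPD in our study population (often with brain damage and perinatal events) is much higher than 50" per cent, and expects at least 50 children (50%) to be at risk.

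**The concern.** The entry rule and the primary endpoint measure different things. A child admitted on the checklist alone may already be within age norms on the variable used to judge the program. The randomised group then mixes two kinds of children: those with a measured processing deficit, in whom RTF change reflects treatment of that deficit, and those without one, in whom any RTF effect would be prevention of later decline or general acceleration.

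A single pooled arm difference cannot tell these apart. A null result could mean that the program does not work, or that much of the group had little RTF deficit to correct. A positive result would not show whether existing deficits improved or later ones were prevented. The Background section gives both as reasons for early habilitation.

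**Working it through.** **1. The plan's own figure.** The power paragraph gives N = 32, power 0.81 and critical F 4.17. The 0.95 quantile of F(1, 30) is 4.171, which agrees with two arms and N = 32. The effect size and the T0–T1 correlation are not stated, so the power itself cannot be reproduced from inputs. Working backwards, power 0.81 at N = 32 needs noncentrality λ = 8.60. With two equal arms λ = N·d²/4, so d = 2·√(8.60/32) = 1.037 SD on RTF change (1.03 gives power 0.805). At the planned 50 children this d gives power 0.95.

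**2. Share entering on the checklist alone.** Let q be the proportion with abnormal RTF (0.09, 0.23 or 0.48).

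(a) Fix the total at risk at the protocol's 50%. Share = (0.50 − q)/0.50:
- q = 0.09: 0.41/0.50 = 82%
- q = 0.23: 0.27/0.50 = 54%
- q = 0.48: 0.02/0.50 = 4%

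(b) Assume a checklist item in p = 50% of children, independent of RTF. At risk = 1 − (1 − p)(1 − q); share = p(1 − q)/at risk:
- q = 0.09: 0.455/0.545 = 83%
- q = 0.23: 0.385/0.615 = 63%
- q = 0.48: 0.260/0.740 = 35%

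With p = 70% the shares in (b) are 88%, 70% and 43%.

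If p = 50%, case (a) is also what results when every child with abnormal RTF has a checklist item. At p = 50%, moving from independence to complete overlap therefore lowers the share from 83% to 82%, from 63% to 54%, or from 35% to 4%. The amount of overlap matters little at q = 0.09 and a great deal at q = 0.48.

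**3. Conditional effect on power at N = 50.** Suppose RTF-abnormal children have the full d = 1.037, RTF-normal children have a fraction k of it, and the SD is the same in both. The pooled effect is d·[1 − share·(1 − k)]. Power is from the noncentral F(1, 48) at alpha 0.05, with the independence shares from (b).

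| Abnormal RTF | Checklist-only share | Pooled d, k = 0 | Power, k = 0 | Power, k = 0.5 |
|---|---|---|---|---|
| 48% | 35% | 0.67 | 0.64 | 0.84 |
| 23% | 63% | 0.39 | 0.27 | 0.69 |
| 9% | 83% | 0.17 | 0.09 | 0.55 |

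Under the fixed-total shares in (a), power with k = 0 is 0.93, 0.38 and 0.10 for q = 0.48, 0.23 and 0.09.

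**4. What separate estimates could deliver.** With the shares in (b), 50 randomised children include about 32, 19 or 8 with abnormal RTF. With variance 1 for RTF change, the standard error of the arm difference in a group of n is √(4/n), and that of the interaction is √(4/n₁ + 4/n₀). Even in the all-or-nothing case (k = 0), interaction power is about 0.40, 0.41 and 0.26.

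**The case against.** - **The target is children at risk, not children with established deficits.** The Abstract, the primary question and the Discussion are all framed this way, and prevention is a declared motive. This stands. A reader might infer that the trial enrols the wrong children, or that the abnormal-RTF subset should become the primary estimate. The document supports neither: a comparison in all allocated at-risk children answers the question it poses.
- **Normal RTF does not mean nothing to treat.** The supplement protocol also draws on the visual function assessment and observation, the general protocol goes to every child, and strabismus and nystagmus are themselves checklist items. Outcome measures lists as primary "quantitative visual parameters (eye tracking-based visual detection and viewing reaction times) and VFA (visual acuity, contrast sensitivity, visual field, ocular motility", although the section on other effects calls the visual function assessment secondary. This stands: the absence of a measured deficit is certain only for RTF.
- **RTF-normal children might still respond.** It is tempting to say that they cannot show an effect. Norms follow developmental trajectories, no floor is documented, and the arms could diverge between 1 and 2 years. Zero effect is an assumption, and the k = 0.5 column shows how much depends on it.
- **The checklist-only route may not dominate.** The 48% comes from children without evidence of brain damage. The section on participant characteristics expects 25–50% at risk. The statement that risk factors are much commoner than 50% is not tied to the four checklist items. Independence is doubtful, and the shares in (b) imply 54.5% to 74% at risk rather than 50%. All this stands, so only a range can be given.
- **Existing features help.** Brain-damage strata overlap one checklist item, and T0 RTF enters the repeated-measures model as an outcome. Neither identifies whether a child had abnormal RTF at entry.
- **An analysis plan may define subgroups.** It is not shown and may do so. The point therefore rests on the mismatch between two rules stated in the article, not on an omission.

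**Conclusion.** The mismatch is real. Children with normal RTF on all stimuli are randomised, RTF change is the primary analysis, and baseline RTF status appears in neither the strata nor the listed covariates. On the protocol's figures such children are about half to over 80% of the randomised group if abnormal RTF is 9% to 23%. If it is 48%, they are 4% (50% at risk in total) to 35% (independence, risk factors in 50%), or 43% with risk factors in 70%.

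The consequence for power is conditional. Power of 0.09, 0.27 or 0.64 at 50 children requires independence, no RTF effect in RTF-normal children, and a back-calculated effect of 1.03 to 1.04 SD assigned wholly to the others. The plan states none of these. The figures are an illustration of sensitivity, not a forecast, and do not show that the trial is underpowered. What holds regardless is that the pooled result cannot separate improvement of an existing deficit from prevention. This supports a cheap addition to the analysis, not a change of population or of the primary comparison.

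**What to change.** 1. Keep the primary comparison in all allocated at-risk children, by intention to treat.
2. In the section on effectiveness of the visual intervention program, add baseline RTF status from T0 (abnormal on at least one stimulus versus normal on all) as a pre-specified factor.
3. As a pre-specified supportive analysis, report the arm effect with its interval within each status, and the arm-by-status interaction. Report the number of children in each status by arm.
4. State the main conclusion for children at risk of VPD. Claim improvement of existing processing deficits only as far as the estimate in the abnormal-RTF children supports it.

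The cost is wording. Status is measured before allocation, so the comparison within each status remains randomised, and no new data, visits or children are needed. The amendment should be dated before the coded groups are analysed. Adjusting for status should also help precision: at an assumed T0–T1 correlation of 0.5, a simulation gave about 13% lower variance for the arm difference in change. The downside is that subgroup estimates rest on few children, intervals will be wide, and the interaction test has low power, so a null interaction must not be read as equal effects.
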